**Discussion:**

Once the predictive values of plaque components and characteristics by VH-IVUS on subsequent clinical outcomes are determined among SVGD patients undergoing PCI, an innovative prediction tool of clinical outcomes for SVGD patients undergoing PCI will be created, which may lead to the development of new methods of risk stratification and intervention guidance.

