### VH-IVUS examination and plaque classification

After administration of heparin (100 U/Kg) and glyceryl trinitrate (100–200 μg), VH-IVUS is performed in SVG and other main coronary arteries before and after PCI. Data is obtained using a 20-MHz, 3.5-French EagleEye phased-array Gold catheter (Volcano Corporation, Rancho Cordova, California, USA) with motorized pullback (0.5 mm per second) from the most distal safe position to guide the catheter. The IVUS grey-scale and Virtual histology analyses are performed offline using the Volcano Image Analysis Software (version 3.0.394,Volcano Corporation, USA) and are not used for PCI guidance or subsequent management. Spectral and amplitude analyses of IVUS backscattered radiofrequency are performed by two experienced interventional cardiologists without knowledge of subsequent clinical events. Angiographic qualitative assessment and quantitative measurements are obtained for SVG. Quantitative IVUS measurements include cross-sectional areas (CAS) of the lumen, the external elastic membrane (EEM), and the plaque and media (EEM CAS minus lumen CAS), lesion length, plaque burden (plaque and media CAS divided by EEM CAS), and plaque volume. Qualitative IVUS assessments include plaque rupture (intraplaque cavity that communicated with the lumen with an overlying residual fibrous cap fragment) and characterization of lesions. On the basis of radiofrequency IVUS, plaque components and morphology are classified into the following four types: fibrous tissue (FT), fibrofatty (FF), necrotic core (NC), and dense calcium (DC). A lesion on IVUS imaging is defined as a plaque burden ≥40% in at least 3 consecutive frames. Consistent with published VH-IVUS classifications [25, 28], such lesions are classified as one of the following: 1) fibrotic plaque, mainly fibrous tissue with < 10% confluent NC, < 10% confluent DC, and < 15% FF; 2) fibrocalcific plaque (FCa), mainly fibrous tissue with > 10% confluent DC but < 10% confluent NC; 3) pathologic intimal thickening (PIT), not meeting FCa plaque definitions and predominantly fibrous tissue; 4) fibroatheroma, > 10% confluent NC, including thick-cap fibroatheroma (ThCFA) and thin-cap fibroatheroma (TCFA).

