### Sample size

We expect CAS of plaque and media 2.9 ± 1.7 mm^2^ among patients with MACEs and 1.9 ± 1.5 mm^2^ among patients without MACEs. It is estimated that the incidence of MACEs is 20% in 3 years after PCI for SVGD. Assuming a 20% drop-out rate, a total of 175 participants are required to provide 80% power, with a two-sided type I error of 0.05.

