### Statistical analysis

Analyses will be made using SAS statistical software (version 9.3) by researchers at the Peking University Clinical Research Institute. Continuous variables will be expressed as mean ± standard deviation or median ± interquartile range (IQR), and t-test or Wilcoxon rank sum test will be used to compare the difference between groups. For categorical variables, the chi-square test/ Fisher’s exact test will be performed. Time-to-event data (MACEs in 3 year after PCI) will be presented as Kaplan-Meier estimates and the primary outcome analysis will be carried out using univariate and multivariate Cox proportional hazards regression models. The ideal cut-off of quantitative indexes of VH-IVUS and the diagnostic accuracy will be determined by the receiver-operating characteristic curve (ROC). A *p*-value < 0.05 will be considered statistically significant in all analyses.

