The current study is subject to several limitations. This is an observational cohort study, confounding effects cannot be ruled out entirely. However, the multivariate Cox proportional regression model will be used to determine the independent effects of VH-IVUS findings on long-term clinical outcomes after adjusting for the impact of baseline characteristics. Second, participants with SVGD who are enrolled in a single center (Cardiovascular Institute, Tianjin Chest Hospital) may not represent the population in China. However, we speculate that the relationship between VH-IVUS findings and clinical outcomes should persist in other SVGD patients undergoing PCI, but with varying magnitudes of association. Third, although VH-IVUS is a widely used method in clinical setting, VH-IVUS has some technological limitations. VH-IVUS TCFA is not equivalent to histopathologic definitions and VH-IVUS tend to over-estimate TCFA compared with histology.

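### The study is sized on one VH-IVUS index with about 28 events, yet one 0.05 threshold covers all analyses of up to 16 overlapping indices, and cut-offs and accuracy come from the same data.

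*Protocol article*

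**What the plan says.** **Sample size.** The calculation uses one index: "We expect CAS of plaque and media 2.9 ± 1.7 mm^2^ among patients with MACEs and 1.9 ± 1.5 mm^2^ among patients without MACEs". On events it states: "It is estimated that the incidence of MACEs is 20% in 3 years after PCI for SVGD". On the total: "Assuming a 20% drop-out rate, a total of 175 participants are required" "to provide 80% power, with a two-sided type I error of 0.05".

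**VH-IVUS examination and plaque classification.** The quantitative measures are the lumen, EEM, and plaque and media areas, with "lesion length, plaque burden (plaque and media CAS divided by EEM CAS), and plaque volume". Plaque rupture, four tissue components and a lesion classification with five end categories follow.

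**Statistical analysis.** The primary outcome is analysed by Cox regression, with one variable at a time and with several together. ROC curves supply the best cut-off and the diagnostic accuracy of the quantitative indices. A p-value below 0.05 "will be considered statistically significant in all analyses".

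**Discussion (limitations).** "the multivariate Cox proportional regression model will be used to determine the independent effects of VH-IVUS findings on long-term clinical outcomes", with adjustment for baseline characteristics.

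**Abstract, Discussion.** Once predictive value has been shown, "an innovative prediction tool of clinical outcomes for SVGD patients undergoing PCI will be created". The Conclusion is softer and says only that such a tool can be made.

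**The concern.** The 80% power and 5% error rate were worked out for one index. The Statistical analysis section does not carry that index forward as the primary predictor. It gives every index the same threshold and the same standing, so any of them could be reported as a significant predictor of MACE. The chance that some index passes when none is predictive is then well above 5%.

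Two further steps push the same way. A Cox model with several VH-IVUS terms and baseline covariates has few events to support it. Cut-offs chosen to perform best in a data set, and judged in that data set, look more accurate than they will in new patients.

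The authors want the results used for risk stratification and to guide intervention. A chance predictor, an over-extreme hazard ratio or an inflated accuracy figure would be carried into that use.

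**Working it through.** **1. The plan's own sample size.** Inputs from Sample size: difference 2.9 - 1.9 = 1.0 mm², SDs 1.7 and 1.5, 20% MACE (so 1:4), two-sided 0.05, 80% power, 20% drop-out.

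- n(MACE) = (1.960 + 0.842)² × (1.7² + 1.5²/4) / 1.0² = 27.1, rounded up to 28
- Total evaluable = 28 × 5 = 140
- Enrolled = 140 / 0.80 = 175

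This reproduces the stated 175 exactly, so 28 events is the plan's own basis. Without any drop-out it would be 175 × 0.20 = 35.

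**2. Count of measures** (VH-IVUS section).

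| Group | Number |
|---|---|
| Quantitative: lumen, EEM, plaque and media areas, lesion length, plaque burden, plaque volume | 6 |
| Plaque rupture | 1 |
| Tissue components | 4 |
| Lesion classes (fibrotic, FCa, PIT, ThCFA, TCFA) | 5 |
| Total | 16 |

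If the components are percentages summing to 100 (one fewer) and the classes form one five-level factor (one fewer), about 16 - 2 = 14 free parameters remain.

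**3. Chance of at least one p < 0.05 when none is predictive.** Under independence this is 1 - 0.95^k. For correlated measures it comes from simulating equally correlated null measures. The correlations are assumptions, because the article gives none.

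| Correlation | 16 measures | 14 measures |
|---|---|---|
| 0 | 56% | 51% |
| 0.3 | 47% | 44% |
| 0.5 | 37% | 35% |
| 0.7 | 27% | 25% |

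The expected number of false positives among 16 is 16 × 0.05 = 0.8 whatever the correlation.

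**4. Events against model size.** 28/16 = 1.75 events per measure, 28/14 = 2 per free parameter and 28/5 = 5.6 with five terms, so even a modest model is thinly supported.

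Expected shrinkage can be approximated by S = 1 + p / (n ln(1 - R²)), with n = 140. This treats MACE as binary. The maximum Cox-Snell R² at 20% incidence is 1 - (0.2^0.2 × 0.8^0.8)² = 0.632. Assume the model explains 15% or 30% of that, so R² = 0.095 or 0.190. Then n ln(1 - R²) = -13.95 or -29.45.

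| Parameters p | S at R² 0.095 | S at R² 0.190 |
|---|---|---|
| 1 | 0.93 | 0.97 |
| 2 | 0.86 | 0.93 |
| 3 | 0.79 | 0.90 |
| 4 | 0.71 | 0.86 |
| 5 | 0.64 | 0.83 |

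A shrinkage of about 0.9 supports one to three parameters.

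**5. Same-data accuracy.** In a simulation of linear models built from independent pure-noise predictors on 28 against 112 patients, the average apparent AUC was 0.63 with 5 predictors, 0.68 with 10 and 0.74 with 16. The true value is 0.50.

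**6. Why one primary index rather than Bonferroni.** The standard error of the planned difference is √(1.7²/28 + 1.5²/112) = 0.351, and 1.0/0.351 = 2.848. Power at 0.05 is Φ(2.848 - 1.960) = 81%. At 0.05/16 = 0.0031 it is Φ(2.848 - 2.955) = 46%. A single named primary index keeps the planned power.

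**The case against.** The strongest case is that a generic sentence is being over-read. The article does not say that 16 indices each get a confirmatory test, or that one significant index confirms the hypothesis. Sixteen is a count of measurements, with built-in dependence: plaque and media area is EEM minus lumen, plaque burden is that area divided by EEM, and the lesion classes exclude one another. The study is observational and exploratory in spirit, and it already has an implicit lead index in the sample size.

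Much of this stands, and it rules out several stronger readings:

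- **A chance predictor is more likely than not.** A reader might infer this from the 56%. That figure needs independence, which the definitions exclude. At every correlation above zero in the table the chance is below one half.
- **All measures enter one model, so it is badly overfitted.** The article gives no number of terms. The amount of overfitting cannot be stated, only how it grows with model size. The R² values above are assumptions.
- **The lack of a covariate list, shrinkage or validation plan is itself an error.** A full protocol or SAP may hold these, and an article commonly leaves them there.
- **An unvalidated tool will be fitted to this cohort.** The Abstract makes the tool conditional, the Conclusion says only that it can be made, and the Statistical analysis section has no step that builds one.

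The objection does not remove what the article fixes. The threshold is stated for all analyses, so the multiplicity question is answered rather than left open. The Discussion claims independent effects of VH-IVUS findings in the plural. The index used for sizing is not named as primary in the endpoint or analysis sections.

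**Conclusion.** The point holds in this limited form. The plan is sized for one test at 5% but applies the same threshold to all analyses, with up to 16 overlapping measures available. If none is predictive, the chance of at least one significant index is roughly 25-47% under assumed correlations of 0.3-0.7, and 56% under independence. That is at least five times the nominal 5%. These figures describe one-at-a-time tests, not terms retained in the adjusted model.

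With about 28 events, an adjusted Cox model with more than a few terms and ROC cut-offs judged in the same data would be over-optimistic. By how much depends on choices that the article does not state.

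The event count is itself uncertain. It could rise, because the MACE definition under Study endpoints adds angina and heart-failure hospitalisation to what the Abstract lists. It could fall, because patients enrolled after December 2018 would have less than 36 months by December 2021, and only 67 of 175 had been enrolled by August 2018. At 35 events, 14 free parameters would still have only 2.5 events each.

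**What to change.** - **Statistical analysis:** name plaque and media area, the index used for the sample size, as the single primary VH-IVUS predictor, tested at two-sided 0.05, and say which Cox model carries that test. Report all other indices as exploratory, or with false-discovery-rate control. Replace the sentence that applies 0.05 to all analyses.
- **Adjusted model:** limit it to the primary index plus one or two covariates fixed in advance, which is two or three parameters. Use a penalised Cox model (ridge or Firth) if more are wanted. At the lower assumed R², three parameters still give a shrinkage of only 0.79, so the optimism correction below is needed in either case.
- **Performance:** report bootstrap optimism-corrected C-index, calibration slope and ROC accuracy, repeating the cut-off selection within each bootstrap sample.
- **Abstract:** describe the tool as a candidate score that needs external validation.

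The cost is revised text and modest programming, with no new patients or data. Fewer indices can be called significant, and the prediction claim becomes softer. The planned power for the primary index is kept.

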### Trial status

The first participant was enrolled in July 2017. As of August 2018, 67 participants have been enrolled and recruitment is ongoing in Tianjin Chest Hospital, China. Treatment and follow-up of all participants are planned to continue until December 2021.

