**Methods/design:**

This is a prospective cohort study conducted in Tianjin Chest Hospital, China. Participants with SVGD referred for PCI will be invited to participate in this study, and will be followed up at 1, 6, 12, 24 and 36 months post-PCI to assess clinical outcomes.

The planned sample size is 175 subjects. We will recruit subjects with SVGD scheduled to receive PCI, aged 18–80 years, with a history of previous coronary artery bypass graft (CABG) surgery more than 1 year ago, and willing to participate in the study and sign informed consent.

The composite primary study endpoint is the incidence of MACEs after PCI for SVGD, including death from cardiac causes, non-fatal myocardial infarction, unplanned target lesion revascularization (TLR) and target vessel revascularization (TVR). The primary outcome analysis will be presented as Kaplan-Meier estimates and the primary outcome analysis will be carried out using a Cox proportional hazards regression model.

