### Baseline assessment and follow-up

After receiving written informed consent, clinical staff will collect demographic and clinical characteristics from all participants. Medical records will be reviewed and related clinical information will be extracted. The data to be collected at baseline include demographic characteristics, medical history (diabetes mellitus, hypertension, hyperlipaemia, stroke, arrhythmia, previous myocardial infarction, PCI or CABG surgery, and medicines for cardiovascular disease), physical examination, clinical presentation (vital signs at hospital admission, onset time of chest pain, duration of chest pain, cardiac function with Killip classification), and smoking history. Cardiac color ultrasound, coronary angiogram, pre- and post-PCI VH-IVUS and 18 lead ECG will be done and used for checking inclusion/exclusion criteria. In addition, blood samples will be collected for laboratory testing, including routine blood, blood biochemistry, fasting glucose, coagulation function, homocysteine, cardiac damage markers (lactic dehydrogenase, creatine kinase, B-type natriuretic peptide, hydroxybutyrate dehydrogenase, troponin H, myoglobin), and inflammatory factors.

Eligible participants will be hospitalized for PCI treatment. In the therapy phase, patients will receive PCI for SVGD using drug-eluting stents. Operation notes (operation date, bleeding volume, medication), thrombolysis in myocardial infarction (TIMI) flow, corrected TIMI frame count (CTFC) and adverse events will be recorded in detail.

All subjects will be followed up at 1, 6, 12, 24 and 36 months after surgery, with MACEs and adverse events assessment collected at each time by clinic visits or telephone interview.

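### The December 2021 end of follow-up cannot give all 175 patients 36 months at the reported recruitment rate; the date, or the stated follow-up, events and power, should be corrected

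*Protocol article*

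**What the plan says.** Four statements in the protocol article bear on this.

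- Follow-up per patient (Baseline assessment and follow-up): "All subjects will be followed up at 1, 6, 12, 24 and 36 months after surgery". Study design and setting gives the same schedule.
- Size (Abstract, Methods/design): "The planned sample size is 175 subjects". The Sample size section bases this on a comparison of plaque and media area between patients with and without MACE, where the "incidence of MACEs is 20% in 3 years after PCI for SVGD", with 20% drop-out, 80% power and two-sided 5% error.
- Analysis (Statistical analysis): MACE over 3 years, shown by Kaplan-Meier and analysed by Cox regression as the primary outcome analysis. Cut-offs for the quantitative VH-IVUS indexes come from ROC curves.
- Calendar (Trial status): the first patient entered in July 2017. "As of August 2018, 67 participants have been enrolled and recruitment is ongoing". Then: "Treatment and follow-up of all participants are planned to continue until December 2021".

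The article gives no end date for recruitment, no planned acceleration or additional centre, and no shorter follow-up for late entrants.

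**The concern.** The 36-month promise and the closing date can both be true only if recruitment ends by December 2018. In August 2018 fewer than two fifths of the patients had been enrolled (67/175 = 38%), after more than a year of recruiting.

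If the date stands, about half the cohort will not have the follow-up that the visit schedule promises. The 20% incidence behind the sample size would then not be fully observed, so fewer events would be available than the stated 80% power assumes. Patients with short follow-up also need explicit handling wherever 3-year MACE is used as a yes/no outcome. If they are treated as event-free, some true events will be misclassified.

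**Working it through.** **1. Reproducing the 175.** Inputs from the Sample size section: means 2.9 and 1.9 mm² (difference 1.0), SDs 1.7 and 1.5, 20% MACE (a 1:4 split), two-sided 0.05, 80% power, 20% drop-out.

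N = (1.960 + 0.842)² × (1.7²/0.2 + 1.5²/0.8) / 1.0² = 7.849 × (14.45 + 2.81) = 135.5.

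Rounding up to whole 1:4 groups gives 28 MACE and 112 without, 140 in total, and 140/0.80 = 175. The stated figure is reproduced exactly. Power at 28 and 112 is Φ(1/SE − 1.96), with SE² = 1.7²/28 + 1.5²/112 = 0.1233. That gives Φ(0.888) = 81.3% (Welch t: 79.3%).

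**2. Accrual.** The article gives months, not days, so I took the extremes.

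- 1 July 2017 to 31 August 2018: 67/14 = 4.79 a month.
- 31 July 2017 to 1 August 2018: 67/12 = 5.58 a month.

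**3. Rate needed.** The last entry date for 36 months is 1 to 31 December 2018, which is 3 to 5 months after the reported count. The remaining 175 − 67 = 108 patients would need 108/3 = 36 to 108/5 = 22 a month, about 4 to 7.5 times the observed rate.

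**4. Outcome at the observed rate (linear accrual assumed).**

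| | 4.79 a month from 1 July 2017 | 5.58 a month from 31 July 2017 |
|---|---|---|
| 175th patient enters | 175/4.79 = 36.6 months: July 2020 | 175/5.58 = 31.3 months: March 2020 |
| That patient reaches 36 months | July 2023 | March 2023 |
| Patients with 36 months by 1 / 31 December 2021 | 81 / 86 | 89 / 95 |
| Last entrant's follow-up by 1 / 31 December 2021 (months) | 16.4 / 17.4 | 20.7 / 21.7 |

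So 81 to 95 of 175 (46% to 54%) can reach 36 months. The conflict remains under every reading of the month boundaries.

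**5. Expected events (constant hazard assumed).** λ = −ln(0.8)/36 = 0.0062 per month. Each patient contributes 1 − exp(−λ × min(36, months available)). Summed over the 175 entry dates, this gives 30 to 32 events, against 175 × 0.20 = 35 with full follow-up. Applying the plan's 20% loss (× 0.8) gives about 24 to 26, against 28.

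**6. Power on the plan's formula, 140 evaluable patients.**

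- 24.2 events: SE² = 2.89/24.2 + 2.25/115.8 = 0.139, power 76.6%.
- 25.7 events: SE² = 2.89/25.7 + 2.25/114.3 = 0.132, power 78.5%.

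Power therefore falls from 81% to about 77 to 78% (Welch t: 79% to about 74 to 76%). This formula compares means and is not a Cox power calculation, but it is the only yardstick that the plan gives. With no drop-out at all, 30 to 32 events among 175 give about 85 to 87%.

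**7. If complete 36-month status were required.** After 20% loss, 0.8 × 81 to 0.8 × 95 = 65 to 76 patients remain, against the 140 needed. Power on the same formula is about 49 to 55% (Welch t: 45 to 51%).

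**The case against.** The strongest reply is that the declared primary analysis is Kaplan-Meier and Cox regression. Both use partial follow-up through censoring, so a common closing date costs only the events that would have occurred late. This stands, and it limits the loss to about 3 to 5 percentage points.

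A reader might infer something stronger: that power falls to about one half, or that the 3-year endpoint is lost. The document does not support this. Nowhere does it restrict analysis to patients with complete 36 months. The t-test and chi-square comparisons are described only as between groups, without defining those groups by 36-month MACE status. ROC is named without saying how censored patients enter, a detail that may be left to an analysis plan not shown here. The figures in step 7 are therefore conditional. They are not baseless, because the sample-size calculation itself compares patients with and without 3-year MACE. Nor is it right to infer that 175 is a wrong number, since it is reproduced exactly.

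Two further points have some force. Linear accrual is extrapolated from a single count that includes the start-up period, so the projection holds only at the reported rate. However, removing the conflict would take at least a fourfold rise within a few months at one centre, and none is described. Also, the 20% drop-out has no stated time base. Late entrants with about 18 months of follow-up have less time to be lost, so 24 to 26 events is on the pessimistic side.

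**Conclusion.** The conflict between the dates is real and rests on the document's own figures. Follow-up ending in December 2021 is incompatible with 36 months for all 175 patients unless the remaining 108 are enrolled by December 2018. The date conflict itself needs no assumption about the hazard.

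The statistical consequence is moderate. Under linear accrual, about half the cohort falls short of 36 months. Adding a constant hazard (20% at 36 months) and the full 20% drop-out, about 2 to 4 of 28 expected events are lost, and power falls slightly below the stated 80%. With less drop-out it could stay above 80%. The loss becomes serious only if some analysis needs complete yes/no status at 36 months. This should be corrected while recruitment is open, but it does not undermine the design.

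**What to change.** Choose one of two changes and make the sections on follow-up, sample size and trial status agree.

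- **Extend.** Define the end of follow-up as 36 months after the last enrolment, about March to July 2023 at the observed rate. The cost is later clinic or telephone contacts for about half the cohort, running some 14 to 20 months beyond December 2021 for the last entrant (36 − 21.7 to 36 − 16.4).
- **Keep December 2021.** State a common closing date with administrative censoring, a minimum follow-up of about 16 to 22 months instead of 36 for all, about 24 to 26 expected events after drop-out, and the power that these give. Keep the ROC objective, but use a censoring-aware (time-dependent) ROC so that patients with short follow-up are not counted as MACE-free. The cost is a slightly less favourable stated power.

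Neither option needs extra patients. In both, update the projected dates and events as actual accrual becomes known.
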